#### Empathy subscale of Adult-Adolescent Parenting Inventory (AAPI-2) [33]

The AAPI-2 has been used in previous evaluations of parenting programmes [34]. A 10-item subscale of the AAPI-2 measuring ‘empathy towards children’s needs’ will be used in the present study. The items assess the understanding and recognition of children’s feelings and needs. Parents are asked to rate their agreement with a statement on a 5-point scale (1 = Strongly Agree, 2 = Agree, 3 = Uncertain, 4 = Disagree, 5 = Strongly Disagree). The range for the total score for this item is 10 to 50, with higher scores indicating greater parental empathy. There are two versions of the inventory (Form A and Form B); for consistency across the three time points, only the empathy subscale of Form A (α = 0.84) will be used in the present study.

#### Alabama Parenting Questionnaire (APQ) [35]

The APQ is a measure of parenting practices. Three of the five subscales will be included in the study: positive involvement with children (10 items, range of possible values for subscale 10 to 50); use of positive discipline techniques (6 items, range of subscale 6 to 30), and consistency in the use of such discipline (6 items, range of subscale from 6 to 30). Each item refers to a parenting practice and respondents are required to indicate how often they typically use each of these practices on a 5-item scale (1 = Never to 5 = Always). The APQ has adequate psychometric properties; the included subscales demonstrate acceptable to good internal consistency (α = 0.67–0.80) [36].

### Other measures

#### Family Demographics Questionnaire (FDQ)

The study will use a short questionnaire to gather basic demographic information about the child and their family. It is adapted from one used in the trial of another parenting intervention [37] and includes variables such as date of birth, age, gender, ethnicity, SEN status, education, members of household, relationship quality, family health and financial situation. The data will be used to describe the sample, examine the extent to which demographic characteristics are balanced between trial arms and carry out attrition analyses (i.e. the extent to which participants who drop out from the intervention and control arms are different on variables such as gender, ethnicity, family type, deprivation).

#### Family Service Use Questionnaire (FSUQ)

The study will use a short questionnaire based on the Client Service Receipt Inventory (CSRI). The CSRI (and versions of it) has been used in over 100 studies since it was first developed in the mid-1980s [38, 39]. The FSUQ will record the receipt of targeted school services and additional services, detailing the typical length and number of contacts, and also whether any of the services received were in relation to the child’s behaviour. It will be used to assess what other services participants in the trial receive and in particular what participants in the control arm receive, as this will help to explain the results (e.g., if there is no impact, it could be because control arm participants received significant extra support from other sources).

### Intervention fidelity

In order to promote fidelity, Malachi provides facilitators with all programme materials for delivery (e.g. manual, exercise materials, and printed posters with agendas and course content). It also provides fidelity instructions in the 3–4 day trainings for facilitators and has a 12-month refresher where the programme content and fidelity tools are reviewed during a 1-day training programme. Fidelity monitoring tools have been developed by Malachi in order to monitor and further promote the high-quality delivery of *Inspiring Futures*, including dose, quality, adherence to the core components of the programme and level of parent engagement. The tools include an attendance register, a self-report checklist for Malachi facilitators and a parent feedback form. Malachi will also use an adapted version of the Parent Programme Implementation Checklist (PPIC), an observational tool which provides a global measure of adherence to core components, the quality of delivery and parent responsiveness [40].

### Data collection

Malachi will obtain the baseline SDQ data from the child’s main parent during an information session at the school (or in a few cases over the phone if the parent is unable to attend the information session). The child’s main parent will provide consent to Malachi for their details to be passed to the Trial Coordinator at the Dartington Social Research Unit (DSRU). An appointment will be made for an independent data collector to visit the family home or child’s school to obtain written informed consent from the main parent to take part in the study. Data collectors will be trained to administer informed consent documents and measures and will complete Level 1 safeguarding training via the NSPCC online course. Data collectors will be supervised by the Trial Manager at the DSRU. The remaining baseline assessments will be collected at that visit (usually within 2 weeks after baseline SDQ), and all follow-up data are collected during home visits. Data will be collected via self-report paper-based questionnaires completed by the main parent. Data collectors will provide assistance to low literacy parents for completing the questionnaires if necessary. Translators will accompany data collectors on visits where parents or children require measures to be administered in languages other than English. Implementation fidelity data will be collected by supervisors at Malachi, and shared with the research team, in line with protocols laid out in the staff handbook. Sessions 4 and 8 in every course will be video-recorded by Malachi (with participants’ consent) and coded using the PPIC by two people working independently (one DSRU, one Malachi) who will then agree a single consistent version.

### Sample size

We aim to recruit 248 participants. This sample will allow us to detect a between-group effect size (ES) of d = 0.40 with 80% power at the 5% level of significance, with allowance for up to 20% loss-to-follow-up.

### Recruitment and retention

Malachi are experienced in working with schools to identify suitable participants for *Inspiring Futures* and will be responsible for recruiting a sufficient number of referrals in order to reach the required sample size. Referrals will be made by a member of school staff (e.g. a teacher or SENCO) who knows the child well and has concerns about the child’s behaviour or emotional well-being. Malachi will screen each referral during an informal information session, which will be held at the school (see ‘Data collection’ above).

Several strategies to minimise attrition will be put in place. The Trial Coordinator will keep regularly updated records in a database to track all study participants. Each participant will be given change of address cards to notify the research team of new contact details and phoned up to three times during the trial to confirm that their contact details are correct. A regular newsletter on the progress of the trial will be distributed to participants, and all families will be offered a £10 gift voucher for each of the three home data collection appointments. Data will be collected from all participants who can be contacted and who consent to participate in data collection, regardless of their level of participation in the intervention.

### Randomisation

An online central computer-randomisation service will be provided by an independent trials unit (Exeter CTU) and will conceal the allocation sequence until assignment to group. The randomisation process will require the Trial Coordinator to log in to a password-protected website and enter the relevant data of each newly recruited participant. The first 25% of the total number of recruits at each site (Birmingham and Somerset) will be allocated by simple randomisation with an allocation ratio of 1:1, and then minimisation will be used to minimise the imbalance between the intervention and control arms in terms of age (< 10 or ≥10 years) and gender. The approach will be dynamic in that each case will be randomised as soon as baseline measures have been completed.

### Blinding

Following randomisation, the Trial Coordinator will notify Malachi by secure electronic communication, and the child’s family and the referrer by standard letter, about the resulting group allocation. The participating family will therefore *not* be blind to allocation. Participants will be aware of the group allocation but will be instructed not to reveal this to the data collector at each follow-up assessment. Data collectors will be blind to group allocation, and will report if they inadvertently become unblinded by participants during a data collection visit. In cases where this occurs at the first follow-up, a different data collector will be assigned to visit the family at the second follow-up where possible. Rates of unblinding of data collectors will be reported with the results of the trial. The FSUQ, which is only administered at the final data collection point (second follow-up), does ask participants – in the last question – to indicate whether or not they received the *Inspiring Futures* programme in whole or in part. The purpose of asking the question is to determine if there is treatment contamination – in other words, if any parents in the control group received *Inspiring Futures*. As this is a self-completion questionnaire, this will not necessarily unmask participants to the data collectors. If it does, however, it is the last question in the final data collection point of the study, and so could not be considered to bias the outcome data. Further, since the outcome data will be collected using self-completion questionnaires rather than through observation or interview (unless a participant requests that the data collector administers the questionnaires in interview style), it is considered unlikely that unblinding data collectors at any point in the study will bias the outcome data. Nevertheless, at the two data collection points where it is relevant (first and second follow-ups) the data collector will be asked to report (i) whether the participant indicated which arm of the trial they are in, and, if so, (ii) which arm it is. The Trial Coordinator will keep and manage the randomisation allocation list in a password-protected document; data collectors will have no access to this list. The statisticians will remain blind to the group allocation.

### Statistical methods

Baseline and demographic characteristics will be summarised using means and standard deviations (or medians and interquartile ranges) for continuous variables and percentage for categorical variables. The comparison of the trial arms will use an intention-to-treat framework with participants analysed according to the trial arm they were randomised to, regardless of whether or not they received the intervention. The primary outcome is the SDQ Total Difficulties score at 32 weeks follow-up. The secondary outcomes are: SDQ Total Difficulties score at 16-weeks follow-up; whether the child scored above the clinically relevant cut-point on the SDQ Total Difficulties scale (i.e. ≥14) (16 and 32 weeks follow-up); the SDQ subscale scores (16 and 32 weeks follow-up); the SDQ Impact Supplement score (16 and 32 weeks follow-up); the ECBI frequency and intensity scales (16 and 32 weeks follow-up); the WCQ subscale scores (16 and 32 weeks follow-up); the AAPI-2 empathy scale (16 and 32 weeks follow-up); and the APQ selected subscale scores (16 and 32 weeks follow-up). The trial arms will be compared in crude (unadjusted) analyses presenting the mean difference for continuous outcomes and odds ratio for binary outcomes. Linear mixed effects models (for continuous outcomes and the binary outcome) will be used with group as a random effect in the intervention arm [41]. Adjustment will be made in these comparisons for the stratification factors (age, gender and trial site), ethnicity, socio-economic status, special educational needs, parent education, parent marital status and the baseline score on the outcome being analysed. The adjusted and imputed (see below) analysis will be considered primary. Subject to having sufficient numbers in the sub-groups, tests of interaction will be used to examine whether the effect of the intervention differs across categories based on age (< 10 versus ≥10 years), gender, ethnicity and level of difficulties on the SDQ Total Difficulties score at baseline (borderline [14 to 16] vs. abnormal [≥17]); 95% confidence intervals and *p*-values will be reported with these estimates. The primary analyses will be based on analyses of 20 multiply imputed datasets to handle missing data. This means that, unless they withdraw consent completely, all randomised participants will be included in the analysis – even if they drop out (refused or unable to contact). Fidelity to the delivery of the intervention programme will be summarised using descriptive statistics. It will be assessed in terms of the different dimensions measured (adherence, dose, quality and engagement). A secondary analysis will be undertaken to quantify the extent to which the intervention effect on the parent SDQ Total Difficulties score at 32 weeks follow-up (the primary outcome) is determined by participation in the intervention (percentage of sessions attended). This will involve a complier average causal effect analysis (CACE) [42, 43] on the complete case data.

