### Participants

The sample will be drawn from approximately 100 mainstream primary schools and children’s centres across the two trial sites in England: Birmingham (c.80) and Somerset (c.20). The former is a large ethnically diverse city while the latter is a large rural county (the trial involves two large towns in the county). The vast majority of referrals (> 90%) are expected to come from schools rather than children’s centres. The minimum number of eligible referred and baselined parents per school needs to be 8 to ensure the minimum viable intervention group size (4) is reached following randomisation. If fewer than 8 parents are recruited from a given school, there is an option to include eligible parents from a nearby school.

Participants will be the parents of children aged 6-11 years at the point of referral (in school years 2 to 6) who are referred by school/centre staff to Malachi’s *Inspiring Futures* Programme. The programme can facilitate the inclusion of partners who are parents of the same child; however, only the main caregiver (as identified by the parents) will report on study outcome measures. Children will be reported to display psychosocial difficulties in the home context, identified by a parent-report ‘borderline’ (or above) Total Difficulties score (i.e. ≥14) on the Strengths and Difficulties Questionnaire (SDQ) [24]. The following exclusion criteria will apply: (i) a parental mental health issue, substance abuse issue or significant self-esteem and/or confidence issue *that would seriously affect their ability to participate in therapeutic group sessions*; (ii) a family situation that does not allow the parent to fully engage in the process (e.g. they do not have enough access to their children to effect change); (iii) other reasons that prevent the parent from participating in the group (not proficient in English, physical health issues, childcare obligations, work commitments); and (iv) parent is already receiving other therapeutic support (e.g. psychotherapy, psychiatry).

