### Group-based element

Parents are invited to attend 10 to 12 (90-min) weekly group sessions (between 4 and 10 parents) at their child’s school facilitated by a pair of Malachi group facilitators. The group sessions run during a school term and the number of sessions depends on the length of the term, but the same content is covered across all groups. The content focuses on helping parents to: understand their children’s needs and the consequences of not meeting them [via child development education]; develop empathy by understanding how children’s thoughts and feelings inform their behaviour; reflect on how their (parents’) parenting behaviours and coping mechanisms affect their ability to meet their children’s needs, and learn how their own experience of being parented (especially adverse experiences) shaped these [using elements of psychodynamic and transactional therapy]; identify and choose to avoid unhealthy default parenting behaviours or maladaptive coping mechanisms (such as the misuse of alcohol or substances, or reckless or self-harming behaviours) and instead pursue more healthy approaches [using solution-focused therapy]; consider how their support network affects their parenting and their children positively or negatively and, if necessary, make changes; and appreciate how conflicts occur and get resolved, their (parents’) default role in conflict and how they can better resolve conflict. Sessions 1 to 7 cover key concepts and theories, sessions 8 to 11 entail participants discussing how to apply their learning in everyday scenarios (these can be consolidated into two sessions), and session 12 includes a recap and discussion of key learning points and the presentation of certificates to parents.

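### The primary model has no term for the school or recruitment set shared by both arms, so its standard error is somewhat too wide if school variance remains after adjustment

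*Protocol article*

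**What the plan says.** All references are to the protocol article.

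- **Random effects (Statistical methods).** Linear mixed models are fitted "with group as a random effect in the intervention arm". No other random term is named.
- **Covariates (same section).** "Adjustment will be made in these comparisons for the stratification factors (age, gender and trial site"), followed by participant-level variables and the baseline score of the outcome. School is not in the list. "The adjusted and imputed (see below) analysis will be considered primary", so this model carries the main result.
- **Recruitment (Participants).** "The minimum number of eligible referred and baselined parents per school needs to be 8", and the reason given is "to ensure the minimum viable intervention group size (4) is reached following randomisation". Where a school yields fewer, "there is an option to include eligible parents from a nearby school".
- **Delivery (Group-based element).** Parents attend "weekly group sessions (between 4 and 10 parents") at the child's school.
- **Allocation (Randomisation).** Individuals are allocated, by simple randomisation for the first quarter at each site and then by minimisation on age and gender. School plays no part.

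**The concern.** A random effect in one arm only suits a trial in which treated participants are clustered by therapy group and controls are unclustered. Here the rule of eight parents to obtain a group of four means that the other parents in the same set become controls. The sets are therefore crossed with arm.

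Anything that a school gives all its families raises or lowers both arms together and largely cancels in the treatment contrast. The article offers two plausible sources: usual support that differs by school (Control arm) and referral by each school's own staff (Recruitment and retention). The stated model cannot credit that cancellation. It counts school variation as group variance in the intervention arm and as independent residual among controls. What is at stake is precision, in a trial planned at 80% power.

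**Working it through.** **1. The plan's own figure.** Sample size gives d = 0.40, 80% power, 5% significance (taken as two-sided) and 20% loss. The calculation gives 99 per arm; 99/0.8 = 123.75, rounded up to 124, so 248 in total. This reproduces the stated figure without any allowance for clustering.

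**2. Set-up.** Let the total variance be 1 = s (school) + g (therapy group) + e (residual). Take K sets with m parents per arm in each, and N = Km per arm. The documents give neither s nor g, so both are assumed. I use K = 25 sets of eight, which is 200 analysed and close to the 198 that the plan expects.

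**3. Formulae for an equal split within each set.**

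- Variance the planned model reports: (s + g)/K + e/N + (s + e)/N
- Actual variance of the contrast: g/K + 2e/N

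With s = 0.05, g = 0, K = 25, m = 4 and N = 100:

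- Planned: 0.05/25 + 0.95/100 + 1/100 = 0.0215, so SE = 0.1466
- Actual: 2 × 0.95/100 = 0.0190, so SE = 0.1378
- Ratio of SEs: 1.064

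**4. Allocation as the protocol describes it.** Equal splits are not guaranteed. Under simple 1:1 allocation, eight parents divide exactly 4:4 with probability 70/256 = 27%. I therefore took the planned model's SE, the actual (sandwich) SE of the same estimator, and the SE of a model with a set effect in both arms, averaged over 300 allocations not stratified by school (g = 0, one school per set):

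| Assumed school ICC | Planned SE | Actual SE | Planned/actual | SE with set term |
|---|---|---|---|---|
| 0 | 0.1417 | 0.1417 | 1.000 | 0.1417 |
| 0.01 | 0.1430 | 0.1417 | 1.009 | 0.1417 |
| 0.02 | 0.1442 | 0.1417 | 1.018 | 0.1416 |
| 0.05 | 0.1476 | 0.1412 | 1.045 | 0.1407 |
| 0.10 | 0.1532 | 0.1402 | 1.093 | 0.1385 |

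Power for d = 0.40, planned model against the model with a set term, is 77% against 81% at ICC 0.05 and 74% against 82% at 0.10. A true group ICC of 0.05 hardly alters the ratios (1.045 at school ICC 0.05, 1.091 at 0.10).

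**5. Sensitivity to set structure.**

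- *Two schools pooled per set, four parents each.* Only 6 + 6 = 12 of the 28 pairs in a set share a school (43%). Repeating step 4 gives an excess of about 0.4%, 0.8%, 1.9% and 3.8% at ICC 0.01, 0.02, 0.05 and 0.10.
- *Larger sets (12 of 16), one school each.* The excess is about 2%, 4%, 10% and 19%.

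In every case with school variance above zero, the planned SE exceeded the actual SE.

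**The case against.** The strongest reply is that the intervention-arm group term already deals with the clustering that could make inference too optimistic, and that what is left out is only an efficiency refinement. That is correct as to direction. The estimate is unbiased and the test is conservative, so a reader who infers a threat to validity goes further than the documents allow.

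A second reply is that the school variance may be negligible. The outcome is rated by parents, all children are selected on the same screening threshold, and the model adjusts for the baseline score and several social variables. This stands: nothing in the article supports an ICC as high as 0.05 or 0.10, and at 0.01–0.02 the excess is 1–2%.

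Third, about 100 schools and centres are named, while 248/8 gives at most 31 sets. If most of them contribute, a set spans about three schools. With a 3/3/2 split, 3 + 3 + 1 = 7 of 28 pairs share a school, so an ICC of 0.05 acts like about 0.0125 and the excess is near 1%. The 100 may be only the pool approached, so this remains a possibility.

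A reader might also infer that the estimated group variance will be misread, because it would contain school variance. The plan does not propose to report or interpret that variance, so no harm follows.

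The reply that this belongs in an analysis plan does not succeed. The article states both the random structure and the covariates, and so fixes the choice.

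**Conclusion.** The point holds in conditional form. The model omits a source of variation that the design shares between arms, and any school variance left after adjustment makes the primary standard error too wide. Under the main assumptions (25 analysed sets of eight, one school per set, allocation not stratified by school), the excess is about 1%, 2%, 4–5% and 9% at ICC 0.01, 0.02, 0.05 and 0.10. It is about half that with two schools per set, and zero with no residual school variance.

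It would be tempting to say outright that the standard error is too wide, or to quote the excess in variance under exact 4:4 splits. Step 3 gives 0.0215/0.0190 = 1.13 on that scale, which is 13% in variance but 6% in SE. The documents support neither: they give no school variance, and allocation is not balanced within school. This is a modest, conservative loss of precision that is cheap to remove.

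**What to change.** Add a random intercept for recruitment set, meaning the school or the pooled schools that share a group, for all participants in both arms. Keep the additional group effect in the intervention arm, since it is still needed. Pre-specify that the model reduces to the one stated if the set variance is estimated at zero or the model does not converge.

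The identifier should already be held, because groups are formed from these sets, so no new data are needed. The article schedules the analyses after its own submission and keeps the statisticians blind to allocation, so the change can be recorded before results are known. The cost is one more variance component, estimated from small sets, with some risk of boundary estimates or non-convergence; the fallback covers this. Adding set to the imputation model is optional and would make the imputation more complex.

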### Design

A two-arm, randomised controlled, parallel group, superiority trial will be conducted to evaluate the effectiveness of Malachi’s *Inspiring Futures* parenting programme in improving behavioural and emotional outcomes in primary school children with elevated psychosocial difficulties. Two hundred fourty eight participants will be randomised with an allocation ratio of 1:1. Parents in the intervention arm will be offered the *Inspiring Futures* programme; parents in both trial arms will have access to services as usual (with the exception of other Malachi services). The trial therefore examines the superiority of the programme relative to a comparator that represents what young people and their families normally receive. Assessments will take place at baseline, 16 weeks after randomisation (first follow-up, post- group parent programme) and 32 weeks after randomisation (second follow-up, post- one-to-one sessions with selected parents) – data will be collected from all participants at this second follow-up, regardless of whether they have received the one-to-one sessions. (See Fig. 2 for an overview of the trial flow chart and assessments.)

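### Effect modification by baseline SDQ and age is tested only on two-category versions of both variables, which costs precision if the effect changes gradually

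*Protocol article*

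**What the plan says.** Statistical methods in the protocol article states that, provided the subgroups are large enough, "tests of interaction will be used to examine whether the effect of the intervention differs across categories based on age" and three further factors. The cut-points are fixed there: the effect is compared according to whether it "differs across categories based on age (< 10 versus ≥10 years), gender, ethnicity and level of difficulties", and the last of these is coded as "level of difficulties on the SDQ Total Difficulties score at baseline (borderline [14 to 16] vs. abnormal [≥17"]). Estimates are to carry 95% confidence intervals and p-values. No interaction with the SDQ score or age on its original scale is described.

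Three other sections bear on this:

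- Participants: children enter if they are "identified by a parent-report ‘borderline’ (or above) Total Difficulties score (i.e. ≥14"), and are aged 6 to 11 at referral.
- Outcome measures: the Total Difficulties score runs from 0 to 40. After entry the lower category therefore holds three score points (14, 15, 16) and the upper holds 17 to 40.
- Randomisation: the age cut at 10 is also a minimisation factor.

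**The concern.** Interaction tests in a trial sized for its main effect are weak to begin with. Splitting a graded variable in two treats all children on one side of the cut as alike, so any trend within a category is lost to the test. For SDQ, everyone from 17 upwards forms one group. A programme whose benefit rose or fell steadily with severity could show a non-significant interaction that a test on the score would have had a better chance of detecting. Because p-values will be reported, readers might take such a result as evidence of no difference by severity or age.

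**Working it through.** **1. The plan's own figure.** Sample size states "This sample will allow us to detect a between-group effect size (ES) of d = 0.40 with 80% power at the 5% level of significance". The number recruited also allows for a fifth of participants being lost. Taking the 5% level as two-sided, n per arm = 2 × (1.960 + 0.842)² / 0.40² = 98.1, so 99 per arm and 198 in total; 198 / 0.80 = 247.5, so 248. The stated number reproduces, and about 198 participants are expected to be analysed.

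**2. How weak the categorical tests are.** With 1:1 allocation, a share s of participants in one category, and the outcome in SD units, SE(interaction) = √(4 / (N s(1 − s))). With N = 198, ignoring clustering and covariates:

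| Share in smaller category | SE | Difference in effects detectable at 80% power |
|---|---|---|
| 50% | 0.284 | 0.80 SD |
| 33% | 0.302 | 0.84 SD |
| 20% | 0.355 | 1.00 SD |

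These are 2 to 2.5 times the design effect of 0.40. Power for a difference in effects of 0.40 SD is 20–29%.

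**3. Information kept by the split.** If the effect changes linearly with X, the two-category test keeps a fraction r² = corr(X, 1[X ≥ cut])² of the information in the continuous test. The protocol gives no distribution for either variable, so the following are assumptions.

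Baseline SDQ: normal, restricted to the whole scores 14 to 40, cut at 17.

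| Underlying mean, SD | Share at 17 or above | r² |
|---|---|---|
| 14, 5 | 57% | 0.58 |
| 14, 6 | 63% | 0.51 |
| 17, 6 | 74% | 0.44 |
| 20, 5 | 84% | 0.36 |
| 20, 6 | 84% | 0.35 |
| 22, 6 | 89% | 0.28 |
| 24, 6 | 93% | 0.22 |

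The range 0.35–0.51 comes from the second to fifth rows. The first row is somewhat better, and the last two show that a more severe sample fares worse.

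Age: uniform from 6 to an upper limit h, cut at 10. With c = (10 − 6)/(h − 6), r² = 3c(1 − c).

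- h = 12: c = 0.667, r² = 0.67
- h = 11.5: c = 0.727, r² = 0.60
- h = 11: c = 0.80, r² = 0.48

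**4. What this does to power.** Take a linear interaction that has 80% power on the continuous scale. With 198 analysed this is about 0.4 SD per SD of the moderator. Power after the split is Φ(2.80 × √r² − 1.96):

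- r² = 0.35: Φ(1.657 − 1.96) = 38%
- r² = 0.51: Φ(2.001 − 1.96) = 52%
- r² = 0.67: Φ(2.288 − 1.96) = 63%

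In sample-size terms, r² = 0.35 is like running the test on 198 × 0.35 = 69 participants, and r² = 0.667 like running it on 132.

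**5. The opposite case.** If the effect steps exactly at 17, or exactly at age 10, the split loses nothing, and a linear test would itself keep only the fraction r².

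**The case against.** The strongest reply is the symmetry in step 5. The efficiency ratio runs both ways, and the documents do not say what shape any moderation takes. The cuts also have reasons: borderline and abnormal are named SDQ bands, eligibility is defined by the lower one, and the age cut is a minimisation factor. They are fixed in advance. The tests are secondary, and the stated objectives and hypotheses include no moderation question. Nor would continuous coding make the tests strong: 80% power still needs an interaction of about 0.4 SD per SD of the moderator.

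All of this stands as a reason to keep the category estimates and to rate the point as minor. It does not make a step at exactly 17 points or exactly 10 years more plausible than a gradual trend, and wanting to display named bands does not require testing on them.

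Three stronger readings are tempting, and the documents do not support them:

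- That the coding simply discards a third to two-thirds of the information. This depends on linear moderation and on distributions that the protocol does not give.
- That the borderline group may be too small, so that the severity test is never done. The plan sets no minimum number, and the distributions behind the 0.35–0.51 range leave about 40 to 91 of 248 children in that band (16% to 37%).
- That children at the extremes of the upper category are being merged in quantity. Under those same distributions, fewer than one child in 248 would be expected to score 38 or more.

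**Conclusion.** The point holds as a minor matter of efficiency. Moderation by baseline SDQ and by age is planned only on two-category versions of variables measured more finely. If moderation is approximately linear, the SDQ test keeps about 0.35 to 0.51 of the information under the central assumptions, and the age test about 0.48 to 0.67. The loss is larger if the sample is more severe, smaller if scores cluster just above entry, and nil if the effect steps at the cut. The power figures further assume 198 analysed and a two-sided 5% test, with no allowance for clustering or covariate adjustment. Only conditional secondary analyses are affected. The primary comparison does not depend on this coding, and nothing in the plan is contradictory here.

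**What to change.** In Statistical methods, or in the analysis plan before unblinding, make arm by continuous baseline SDQ and arm by continuous age the interaction tests. Fit them in the adjusted model, with the corresponding continuous main effects included, and do not make them conditional on subgroup numbers. Report the estimated intervention effect with its 95% confidence interval at a few representative scores and ages. Keep the prespecified borderline/abnormal and under-10/10-or-over estimates, with their 95% confidence intervals, as the accompanying display and as a check on linearity.

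The cost is a sentence or two in the plan and no new data: the SDQ score is already collected and the baseline score is already a covariate, and age and date of birth are on the demographics questionnaire. The downside is that the test assumes an approximately linear trend and would be the less efficient choice if the effect really changed abruptly at the cut. The retained category estimates would let a reader look for that.
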